### Statistical analysis

General principles

1. There are no treatments associated with POST-RENAL, as it constitutes an extended follow up of survivors from a previous randomized trial. However all primary and secondary outcomes will be analysed as according to original randomization in the RENAL Study as well as a cohort.
2. All tests are two-sided and the nominal level of alpha will be 5%.
3. All statistical analyses will be unadjusted except where indicated.
4. Subgroup analyses will be carried out irrespective of whether there is a significant effect of treatment on the primary outcome.
5. We will not impute missing values unless specified otherwise. We will report the number of observations used in the analysis.
6. P-values will not be adjusted for multiplicity. However the outcomes are clearly categorized by degree of importance (primary, secondary and tertiary) and a limited number of subgroup analyses are pre-specified.

Baseline characteristics of patients

Description of the following baseline characteristics will be presented by treatment group. Data for Day 90 survivors will be extracted from RENAL study database. Discrete variables will be summarized by frequencies and percentages. Percentages will be calculated according to the number of patients for whom data are available. Where values are missing, the denominator (which will be less than the number of patients assigned to the treatment group) will be stated in either the body or a footnote in the corresponding summary table. In some instances, additional frequencies and percentages of patients in each category will be reported as indicated in the list below. Continuous variables will be summarized by use of standard measures of central tendency and dispersion using mean and standard deviation as well as quantile points at 0.25, 0.5 and 0.75 where appropriate.

1. Sex
2. Age
3. Weight
4. Percentage of patients with measured weight, percentage of patients with estimated weight and method of weight estimation.
5. Source of admission to ICU (emergency department, hospital floor, another ICU, another hospital, operating room (OR) following emergency surgery, OR following elective surgery, readmission to the same ICU during same hospitalization)
6. Operative or non-operative admission
7. Operative admission diagnosis (number and % in categories a-k)
   1. Cardiovascular
   2. Respiratory
   3. GIT
   4. Neurological
   5. Trauma without traumatic brain injury
   6. Traumatic brain injury +/- multiple trauma
   7. Burns
   8. Renal
   9. Gynecology
   10. Other orthopedic
   11. Other surgical
8. Non-operative admission diagnosis (number and % in categories a-l)
   1. Cardiovascular
   2. Respiratory
   3. GIT
   4. Neurological
   5. Sepsis
   6. Trauma without traumatic brain injury
   7. Traumatic brain injury +/- multiple trauma
   8. Metabolic
   9. Haematological
   10. Burns
   11. Renal
   12. Other medical
9. Severe sepsis at baseline
10. APACHE III score
11. SOFA score
    1. Cardiovascular domain
    2. Respiratory domain
    3. Hepatic domain
    4. Haematologic domain

(SOFA score domains will be analyzed as continuous variables and as categorical variables divided into normal function (SOFA score 0) dysfunction (SOFA score 1-2) and failure: SOFA score 3-4).

1. Last serum urea concentration before randomization
2. Last serum creatinine concentration before randomization
3. Haematological variables
4. Biochemical variables
5. Treatment with mechanical ventilation
6. Estimated glomerular filtration rate (eGFR)
7. Presence of an estimated glomerular filtration rate (eGFR) <60 ml/min

The eGFR will be calculated using the revised modification of diet in renal disease (MDRD) equation[^9^](#_ENREF_9):

eGFR = 175 × (SCr x 0.0113)^-1.154^ × (age)^-0.203^ ×((0.742 [if female]))

SCr is serum creatinine level in micromol/L

Primary analysis

The primary outcome of mortality will be reported as a survival analysis from the time patients are randomized into the RENAL study. Survival curves and estimated median survival time and its 95% confidence interval will be generated according to the Kaplan-Meier method. Data will be censored at the time when the patient was last known to be alive or to be discharged from hospital. Log-rank test will be used to assess the difference between the two survival curves.

Multivariate Cox model will be performed to provide an adjusted long term survival curve of survivors of acute kidney injury. To determine which variables to include in the multivariate Cox model, we will run first a univariate Cox regression on each baseline variable and select variables with a p-value <= 0.01.

The number of events and the median survival (if available including 95% CI) will also be reported.

Secondary analysis

Time-to-event (Time to first return to dialysis beyond Day 90, Time-to-specific cause of death) will be analysed using the same principles as in the primary outcome. Because the two events Death and First return to dialysis are competing events, data will be censored at the time of competing event if it occurs first. Log-rank test will be used to assess the difference between the two survival curves.

As this cause-specific analysis can potentially be biased due to the presence of different cause of death, a competing risk analysis will also be undertaken if the number of competing events (Death and return to dialysis) occurring is moderate to large (e.g. > 10%). This could typically be based on the CIF and the Gray’s test.

For binary secondary outcomes (i.e. Requirement for treatment for high blood pressure), a standard Chi-square test will be used to assess the effect of treatment. Frequencies and percentages per arm, possibly a relative risk (or odds-ratio) measuring the treatment effect and its 95% CI will also be reported along with the p-value of the chi-squared test.

Continuous secondary outcomes (i.e. time to free requirement for dialysis, Blood pressure, Renal function: as measured by serum creatinine and eGFR and Proteinuria, as measured by urine albumin:creatinine ratio) will be summarized by use of mean and standard deviation as well as quantile points at 0.25, 0.5 and 0.75 reported. Comparison in differences in mean between the two groups will be carried out using univariate/multivariate linear regression.

Quality of life: as measured by two measures (EQ-5D and SF-12)

Descriptive statistics of individual responses to the 5 EQ-5D questions and to the 12 SF-12 questions by treatment allocation will be provided. Statistics will include the difference in mean score between the two group.

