This study will extend the follow up of survivors from the RENAL Study to a median of 3.5 years to provide high quality evidence regarding the long term consequences of an episode of severe AKI which represents a serious gap in our knowledge. The follow up will focus upon the mortality rates along with the frequency of markers for future renal and cardiovascular disease such as blood pressure, renal function, urinary abnormalities and quality of life.

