### Study objectives

Primary Objective

The primary objective of the POST-RENAL Study is to compare long-term overall survival of adult patients with acute renal failure according to treatment allocation in the RENAL study.

Secondary Objectives

The secondary outcomes will include:

1. Dialysis free days (for all patients at the start of RENAL study, for patients alive at Day 28, for patients alive at Day 60 and patients alive at Day 90)
2. Time to first return to dialysis beyond Day 90 (death censored)
3. Causes of death, competing risk of dialysis/Death
4. Blood pressure and requirement for treatment for high blood pressure
5. Renal function: as measured by serum creatinine and eGFR
6. Proteinuria, as measured by urine albumin:creatinine ratio
7. Quality of life: as measured by two measures (EQ-5D and SF-12)

In this study, adverse events are likely to be extremely rare due to lack of a study intervention beyond data collection. However it is possible for adverse events to arise from the interactions required for participation in the study (eg. resulting from procedure of blood collection) and these will be reportable to the coordinating centre and local ethics committee where applicable.

1. Number of events and number and proportion of patients experienced serious adverse events

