### Study population

The study population is that of all patients alive at 90 days following randomization in the RENAL study (the primary outcome of that study). Accordingly, the POST-RENAL study will seek to operate in the same centres. The RENAL Study randomized 1508 patients in 35 centres in Australia and New Zealand.

The outcomes of the RENAL Study at 90 days post randomization has been ascertained on 97.1% (n=1464) of participants with 55% (n = 810) of these patients surviving. The first patient was enrolled in the study in December 2005 and the last in August 2008. We will follow up all patients alive at 90 days following randomization at median 3.5 years (+/- 6 months) post randomization.

Follow up will be sought on all survivors from July 2010. Where the patient has died beyond the 90 day follow up of the study, limited data on important events (requirement for dialysis, date of death, cause of death) will be sought. Those who are still alive at the time of extended follow up will be asked to consent to the full data collection.

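### The primary censoring sentence does not say whether hospital discharge is itself a censoring event; applied literally, it would defeat the long-term survival analysis

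*SAP*

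**What the plan says.** The SAP's primary objective is to "compare long-term overall survival of adult patients with acute renal failure according to treatment allocation in the RENAL study". Under Statistical analysis, Primary analysis, mortality is to be "reported as a survival analysis from the time patients are randomized into the RENAL study", using Kaplan-Meier curves, a log-rank test and a Cox model. The censoring rule is one sentence: "Data will be censored at the time when the patient was last known to be alive or to be discharged from hospital". It does not say that the later date applies, or that discharge is used only when nothing later is known.

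Under Secondary analysis, time to first return to dialysis beyond Day 90 and time to cause-specific death "will be analysed using the same principles as in the primary outcome".

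The Study population section sets the follow-up: "We will follow up all patients alive at 90 days following randomization at median 3.5 years (+/- 6 months) post randomization". For patients who died after Day 90, it also plans to obtain the date and cause of death and any need for dialysis. Under Tables and Figures, Figure 2 plots return to dialysis after Day 90 and Figure 3 plots death among Day-90 survivors.

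**The concern.** In a study that traces patients for years, discharge is neither the end of follow-up nor a loss to follow-up. If it is a censoring time, two consequences follow without any assumed figures.

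- A death after discharge falls after the patient's censoring time and is not an event. The deaths that this extended follow-up was set up to find would mostly drop out.
- Censoring is informative. Patients leave hospital because they are recovering, so the risk set is progressively reduced to those still ill enough to stay. Kaplan-Meier assumes that those censored have the same future risk as those who remain. Here their risk is lower, so estimated survival is too low.

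The log-rank test and the Cox model would then describe mortality in hospital rather than long-term survival. The secondary outcomes would fare no better: a patient discharged before Day 90 would be censored before time to dialysis beyond Day 90 begins to count.

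**Working it through.** **1. The plan's own counts.** The Study population section gives "The RENAL Study randomized 1508 patients in 35 centres in Australia and New Zealand" and Day-90 status for "97.1% (n=1464) of participants with 55% (n = 810) of these patients surviving".
- 1508 × 0.971 = 1464.3, which agrees with 1464.
- 810 / 1464 = 0.553, which agrees with 55%.
- Dead by Day 90: 1464 − 810 = 654. Day-90 status unknown: 1508 − 1464 = 44.

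**2. Late deaths at stake.** The SAP gives no mortality figure beyond Day 90, so a range is assumed.

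| Assumed share of the 810 dying between Day 90 and 3.5 years | Late deaths | All deaths | Late share | True survival at 3.5 years |
|---|---|---|---|---|
| 20% | 810 × 0.20 = 162 | 654 + 162 = 816 | 20% | 0.553 × 0.80 = 0.44 |
| 30% | 810 × 0.30 = 243 | 654 + 243 = 897 | 27% | 0.553 × 0.70 = 0.39 |
| 40% | 810 × 0.40 = 324 | 654 + 324 = 978 | 33% | 0.553 × 0.60 = 0.33 |

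**3. Direction of the bias, by hand.** Suppose half of the 654 deaths (327) occur first, then half of the 810 survivors (405) are discharged and censored, then the other 327 deaths occur in hospital.
- Before the discharges: (1464 − 327) / 1464 = 0.777.
- At risk afterwards: 1464 − 327 − 405 = 732.
- Over the remaining deaths: (732 − 327) / 732 = 0.553.
- Kaplan-Meier estimate: 0.777 × 0.553 = 0.43, where the true value is 0.553.

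The first 327 deaths are weighted correctly. The second 327 are divided by a risk set from which 405 survivors have been removed.

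**4. Simulation over a range of discharge times.** The SAP gives no discharge times. The assumptions, with n = 1464, are:
- the 654 early deaths all occur in hospital, with exponential times of scale 20 days truncated at Day 90;
- survivors' discharge times are lognormal with log-SD 0.7;
- late mortality is 20% to 40%.

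| Assumed median discharge of survivors | Day-90 survival, full follow-up | Day-90 survival, censored at discharge | Survivors still at risk after Day 90 |
|---|---|---|---|
| 20 days | 0.553 | about 0.14 | about 13 of 810 |
| 30 days | 0.553 | about 0.32 | about 47 of 810 |
| 45 days | 0.553 | about 0.45 | about 131 of 810 |

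With log-SD 0.6, the results for medians of 20 and 45 days are about 0.07 and 0.44, so the overall range is roughly 0.07 to 0.45. Censoring at discharge leaves about 654 to 657 deaths in all, of which about 0 to 3 fall after Day 90. Full follow-up counts 816 to 978.

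**5. Literal rule against the rest of the SAP.** The objective is long-term survival, follow-up is a median of 3.5 years, dates of late deaths are sought, and Figures 2 and 3 start from Day 90. With so few survivors left at risk at Day 90, neither figure could usefully be drawn. No other section says how the two dates rank.

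**The case against.** The strongest reply is grammatical. The words for last knowledge can govern both halves of the sentence: last known to be alive, or last known to have been discharged. A discharge record is then simply one form of evidence that the patient was alive on that date. The objective, the tracing of late deaths and the planned figures all favour this parse, and an analyst is unlikely to discard deaths collected for the purpose. The practical effect would then be confined to patients with no contact after discharge.

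Much of this stands. A reader might infer from the sentence that the study will discard its late deaths, or that its published curve must be too low. The document does not support that: it contains an ambiguous rule, not a decision to ignore the follow-up. Nor does it say anything about discharge times by arm, so it gives no ground for claiming a bias towards either treatment group. The objection is also right that any single figure for the distortion is one point in a wide, assumed range.

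It does not remove the defect. On the benign parse the discharge clause is redundant, because the last date known alive already covers it. On the other parse it is an error. The sentence permits two different primary datasets, and the SAP does not choose between them.

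**Conclusion.** The point holds as an ambiguity in the rule that defines the primary outcome, with a serious consequence under one of its two readings. That reading probably was not intended.

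The loss of post-discharge deaths follows from the literal rule alone. The downward bias needs only that discharged patients have a lower risk of death than those still in hospital. The sizes are worst-case illustrations:
- Day-90 survival of roughly 0.07 to 0.45 instead of 0.55 rests on assumed median discharge between 20 and 45 days, an assumed spread, and all early deaths occurring in hospital.
- The loss of nearly all of about 160 to 330 late deaths (20% to 33% of all deaths) rests on 20% to 40% of the 810 survivors dying by 3.5 years.

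Under the benign reading these losses do not arise. The secondary time-to-event outcomes stand or fall with the primary rule.

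**What to change.** Replace the censoring sentence under Primary analysis with wording such as:

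> *Patients not known to have died will be censored at the latest date on which they were known to be alive from any source, including POST-RENAL follow-up. The date of hospital discharge is used only when it is that latest date. Deaths after discharge count as events.*

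This keeps discharge as a fallback for patients with no later information, which may include some of the 44 whose Day-90 status is unknown. Because the secondary analyses refer back to the primary one, the same text settles how discharge is treated there; their separate rule of censoring at the competing event is unaffected. The cost is a few lines of SAP wording, with no new data and no change to the planned tests.

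### The primary comparison by RENAL allocation is tested only by an unadjusted log-rank test; a pre-specified covariate-adjusted allocation effect is a cheap addition, with a gain that is probably small

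*SAP*

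**What the plan says.** The primary objective (SAP, Study objectives) is to "compare long-term overall survival of adult patients with acute renal failure according to treatment allocation in the RENAL study". Under Statistical analysis, Primary analysis, survival is counted from RENAL randomisation, described by Kaplan-Meier curves and tested as follows: "Log-rank test will be used to assess the difference between the two survival curves". General principle 3 sets the default: "All statistical analyses will be unadjusted except where indicated". Nothing is indicated for the primary test.

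The next paragraph of Primary analysis brings in the only adjusted survival model: "Multivariate Cox model will be performed to provide an adjusted long term survival curve of survivors of acute kidney injury". For its covariates, "we will run first a univariate Cox regression on each baseline variable and select variables with a p-value <= 0.01". Allocation is not mentioned as a term in this model, and no adjusted hazard ratio for allocation is promised.

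The baseline list includes age, severe sepsis, APACHE III, SOFA domains and mechanical ventilation. On their source the SAP says: "Data for Day 90 survivors will be extracted from RENAL study database". That sentence covers survivors, but Table 1 is planned for both RENAL and POST-RENAL patients, so the data appear to be at hand for the whole randomised set. General principle 5 adds: "We will not impute missing values unless specified otherwise". The SAP states no power, target effect or event number.

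**The concern.** In a time-to-event comparison with many deaths, leaving out covariates that predict death pulls the estimated hazard ratio towards 1 and lowers the power of the test. Here the number of patients is fixed by a finished trial, so the analysis is the only place where precision can still be gained.

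The SAP holds suitable pre-randomisation variables and fits a Cox model, but does not use either for the allocation question. As written, that model cannot stand in for an adjusted comparison: allocation need not be in it, and covariates chosen by p-value from the same data are not fixed in advance. At stake is how informative a null primary result would be.

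**Working it through.** **Head counts in the SAP.** 0.971 × 1508 = 1464.3 (stated 1464). 810/1464 = 55.3% (stated 55%). Deaths by day 90: 1464 − 810 = 654, or 44.7% (stated 45%). These reproduce. There is no stated power to reproduce.

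**Events and nominal power.** Assume that 10% to 50% of the 810 die later. Total deaths d are then 654 + 81 = 735 up to 654 + 405 = 1059; at 30% they are 654 + 243 = 897. With assumed 1:1 allocation and two-sided 5%, power = Φ(|ln HR| × √(d/4) − 1.96). For HR 0.85 and d = 897: 0.1625 × 14.98 − 1.96 = 0.47, so power is 68%. Across the range it is 60% (735) to 75% (1059). The hazard ratio detectable with 80% power is 0.81 to 0.84.

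**Scenario A: constant hazard ratio from randomisation.** Simulation with n = 1464, about 897 deaths, conditional HR 0.85, and one normal prognostic score whose SD on the log-hazard scale is assumed; 2000 runs. The last two columns drop patients at random for a missing covariate.

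| Score SD (C-index) | Log-rank | Adjusted Cox | Gain, points | Adjusted, 10% dropped | Adjusted, 20% dropped |
|---|---|---|---|---|---|
| 0.3 (0.58) | 64% | 67% | 3 | 62% | 57% |
| 0.5 (0.61) | 63% | 69% | 6 | 64% | 60% |
| 0.7 (0.67) | 55% | 68% | 13 | 63% | 58% |
| 0.9 (0.72) | 47% | 68% | 21 | 63% | 58% |

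At HR 1 (SD 0.7) the rejection rates were 5.2% (log-rank) and 5.3% (adjusted), so adjustment does not inflate type I error.

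**Does Scenario A fit what the SAP already reports?** Background and rationale gives 45% mortality at 90 days in both groups. Ignoring covariates, HR 0.85 from day 0 with about 45% dead overall means survival of, say, 0.525 in one arm and 0.525^0.85 = 0.578 in the other. Mortality is then 47.5% against 42.2%, a gap of about 5 points. The standard error of that difference is √(4 × 0.447 × 0.553/1464) = 2.6 points. Equal mortality is therefore about two standard errors from Scenario A, which is not excluded but is a poor fit.

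**Scenario B: no effect to day 90, then an effect.** Simulation with n = 1464, 31% late deaths assumed, score SD 0.4, 0.6 and 0.8; 800 runs each. Log-rank against adjusted Cox, from randomisation:
- HR 0.75 after day 90: 18 v 19%, 18 v 18%, 16 v 17%.
- HR 0.85 after day 90: 9 v 9%, 11 v 9%, 9 v 11%.

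The Monte Carlo standard error of a single figure is about 1 point (√(0.1 × 0.9/800) = 0.011), so differences of 2 points either way are noise. A further simulation of late effects gave about 1 to 3 points. The gain from randomisation is therefore about 0 to 3 points. Among the 810 day-90 survivors alone it is about 2 to 8 points.

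**The case against.** The strongest reply is that nothing here is wrong. The log-rank test is valid under randomisation, matches the primary objective and needs no covariate choices. Chance imbalance in severity is already allowed for in its type I error. All of this stands, and it limits the point to a suggestion for better efficiency.

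The second reply is that the large gains come from a constant hazard ratio of 0.85 from randomisation, which sits badly with equal day-90 mortality. This also stands. A reader might infer from Scenario A that the plan forgoes 10 to 20 points of power. The documents do not support that: prognostic strength, effect size and late mortality are all assumed, and the one relevant result they report points towards the small gains of Scenario B.

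Third, adjustment is not free. Without imputation, losing 10% of patients to missing covariates removes the gain for weak covariates, and losing 20% reverses it for weak to moderate ones. The SAP gives no missingness rate. This can be met, because principle 5 allows imputation where it is specified, so a fill-in rule keeps every patient. Two costs remain: the adjusted hazard ratio is conditional on the covariates and differs numerically from the unadjusted one, and the list would be fixed after day-90 results by arm were known. Both are small if the log-rank test is kept alongside.

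The planned Cox model is no full answer, since nothing in the text gives it the task of estimating the allocation effect.

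**Conclusion.** The point holds as a cheap improvement. The only stated test of allocation on the primary outcome is unadjusted. The one adjusted survival model is neither said to include allocation nor fixed in advance, although plausible prognostic baseline variables are already held.

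The size is uncertain: about 3 to 21 points of power under a constant HR of 0.85 from randomisation, but about 0 to 3 points (about 2 to 8 among the 810 day-90 survivors) if any effect starts after day 90. The second range fits the reported equal day-90 mortality better. Both rest on assumed 1:1 allocation, late mortality, effect size and prognostic strength, and on complete covariates.

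It would be a mistake to conclude that the primary test is invalid, or that a null log-rank result could not be trusted.

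**What to change.** Add to Primary analysis a pre-specified Cox model with RENAL allocation and a short fixed list of pre-randomisation covariates: age and APACHE III (both continuous), severe sepsis at baseline and mechanical ventilation. State that the list is not chosen by p-value. Give a simple single-value rule for missing baseline covariates, as principle 5 permits, so that no patient is dropped. Report the adjusted hazard ratio for allocation with its 95% CI. Keep the log-rank test and Kaplan-Meier curves, and keep the descriptive adjusted survival curve as a separate item.

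The cost is a few sentences of SAP text and one extra model on data already held. The report should say that the adjusted hazard ratio is conditional, and that the covariates were fixed after the day-90 results by arm were known.

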### Background and rationale

The incidence of Acute Kidney Injury (AKI) is increasing with overall rates exceeding that of end-stage kidney disease by a factor of 15-fold[^1-3^](#_ENREF_1). In its most severe form, where patients require dialysis in an ICU, the mortality is over 50%[^3^](#_ENREF_3)^,^[^4^](#_ENREF_4). There are no treatments proven to reduce this mortality and there is little long term follow up data from large studies of survivors from an episode of severe AKI.

Beyond the mortality of AKI, the long term renal outcomes of survivors of AKI remain unclear. One small case series[^5^](#_ENREF_5) suggested relative preservation of renal function in survivors of AKI but there is very little data beyond hospital discharge. The VA/NIH trial reported very high rates of renal failure and dialysis dependence in the surviving patients, with 75% of survivors showing no recovery of renal function by day 28[^6^](#_ENREF_6). In addition a recent publication linking hospital admissions data with the US Renal Data System Registry [^7^](#_ENREF_7) suggests that patients with AKI had a 13 fold increase in the risk of developing end stage kidney disease over the following 2 years. This risk rose to 42 fold if the patient had chronic kidney disease in addition to an episode of AKI. These recent studies of large numbers of patients raise very serious concerns about the long term renal outcomes of AKI. However, the evidence is limited by the small numbers, short follow up and reliance upon admission coding data. There is no prolonged follow up assessment of a large cohort of patients with AKI from a randomized controlled multi-centre study.

The RENAL Study, an NHMRC funded multi-centre RCT, is the largest study of AKI treatment and randomized 1508 patients to two different dialysis dose intensities in 35 centres across Australia and New Zealand. It completed follow up on 97.1% of randomized patients out to 90 days[^8^](#_ENREF_8). There were no differences in patient mortality between the normal and augmented intensity dialysis groups and the mortality in both groups was 45%. The large numbers of patients enrolled in the RENAL Study, the demonstrated completeness of data and the absence of such follow up from the literature represent an unprecedented opportunity to define the long term outcomes of AKI in a unique manner.

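### The adjusted survival model picks its covariates only by univariable p <= 0.01, a rule that can lose moderate prognostic factors and gives an unstable covariate set

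*SAP*

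**What the plan says.** The rule is in the SAP under Statistical analysis, Primary analysis. The purpose of the model is stated first: "Multivariate Cox model will be performed to provide an adjusted long term survival curve of survivors of acute kidney injury". The covariate rule follows: "we will run first a univariate Cox regression on each baseline variable and select variables with a p-value <= 0.01". The SAP gives no other rule for this model. It names no covariate that is always included, and describes no shrinkage, stability check or allowance for selection.

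The randomized comparison is separate. The preceding paragraph says "Log-rank test will be used to assess the difference between the two survival curves", and General principles adds "All statistical analyses will be unadjusted except where indicated". General principles also sets a two-sided 5% level for tests and states "We will not impute missing values unless specified otherwise".

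The candidates are whatever counts as a baseline variable. The list under Baseline characteristics of patients includes:
- two unspecified groups, the haematological and the biochemical variables;
- eGFR, and also an indicator for eGFR below 60;
- operative or non-operative admission, an 11-category operative diagnosis, a 12-category non-operative diagnosis, and an admission source that itself distinguishes emergency from elective surgery.

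**The concern.** Screening each variable alone at a strict threshold asks whether this sample gives strong marginal evidence. It does not ask whether the variable belongs in the model. Three consequences follow.

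- A factor of moderate size can fail the screen by chance, leaving the adjusted curve under-adjusted. Age, APACHE III and severe sepsis must compete like everything else. The 0.01 cut-off is stricter than the SAP's own 5% level, so a factor that is significant by the SAP's standard can still be excluded.
- The set that survives varies from sample to sample. Overlapping candidates can enter together, and the open-ended groups leave the pool itself undefined. Operative diagnosis has meaning only for operative admissions and non-operative diagnosis only for the rest. With no imputation, the SAP does not say how both could enter one model.
- If intervals are reported for the selected coefficients or for predictions, they would be computed as though the model had been fixed in advance.

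At stake is the credibility of the only adjusted cohort analysis of the primary outcome. The test by allocation is not at stake.

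**Working it through.** **Cohort counts.** Study population reports outcomes "ascertained on 97.1% (n=1464) of participants with 55% (n = 810) of these patients surviving". Check: 1464/1508 = 97.1% and 810/1464 = 55.3%. Both agree with the SAP to its rounding.

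**Inputs for the screen.** The threshold of 0.01 (two-sided critical value 2.576) and the 810 survivors come from the SAP. The SAP gives no deaths after day 90, so I assume 20%, 30% and 40% of 810, that is 162, 243 and 324. Prevalence and hazard ratios (HR) are also assumptions.

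**Chance that a binary factor is retained.** With D deaths and prevalence p, SE(log HR) = 1/sqrt(D p(1-p)), Z = ln(HR)/SE, and
Pr(retained) = Phi(Z - 2.576) + Phi(-Z - 2.576).

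For D = 243 and p = 0.2, SE = 1/sqrt(243 x 0.16) = 0.160. HR 1.5 gives Z = 0.405/0.160 = 2.53 and 48%. HR 1.3 gives Z = 0.262/0.160 = 1.64 and 17%.

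| Deaths (assumed) | HR 1.5 | HR 1.3 |
|---|---|---|
| 162 | 30% | 11% |
| 243 | 48% | 17% |
| 324 | 63% | 25% |
| about 900 | 99% | 72% |

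The last row takes every patient with a known day-90 outcome from randomization: 1464 - 810 = 654 deaths by day 90, plus 243 later, gives 897.

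**Continuous factors.** The same formula with variance 1 (HR per SD) gives Z = ln(HR) x sqrt(D).

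| Deaths (assumed) | HR 1.10 | HR 1.15 | HR 1.20 | HR 1.30 |
|---|---|---|---|---|
| 150 | 8% | 19% | 37% | 74% |
| 250 | 14% | 36% | 62% | 94% |
| 350 | 21% | 52% | 80% | 99% |
| 900 | 61% | 95% | 100% | 100% |

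**Stability.** The rule was simulated with 20 candidates and 300 replicates per scenario. Eight candidates were real (HR per SD 1.5, 1.3, 1.2, 1.2, 1.15, 1.15, 1.1, 1.1) and 12 were null. A null treatment was forced into the model. With 810 patients, about 290 deaths and uncorrelated candidates:
- on average 3.9 of the 8 real factors were dropped, and all eight were never kept together;
- 85 different covariate sets arose in 300 replicates, and the commonest had an 11% share;
- two replicates shared on average 56% of their combined covariates (Jaccard index).

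The mean number of real factors dropped was 5.0 at about 165 deaths, 3.2 at about 380 and 1.3 at about 900 (1464 patients).

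**Intervals, if reported.** With uncorrelated candidates and 810 patients, nominal 95% intervals for the selected coefficients covered 89% to 93%. For a patient's linear predictor, coverage was 54% at about 290 deaths and 74% at about 900. A fixed model with all 20 candidates covered 94% to 95%.

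**Treatment effect.** Coverage for the null treatment effect stayed at 94% to 96% in every scenario.

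**The case against.** The strongest reply is that this is a supporting, descriptive model with an explicit, pre-specified rule, and that little rests on it. Much of that stands, and it rules out several stronger readings that a reader might infer.

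- *That the primary result is biased, because the rule sits under Primary analysis.* The documents do not support this. The comparison by allocation is an unadjusted log-rank test that the screen does not touch.
- *That the adjusted curve and its hazard ratios are main results.* The SAP promises a curve from this model but no hazard ratios. Tables and Figures lists three Kaplan-Meier graphs and one cumulative incidence figure, and no adjusted figure.
- *That the plan will publish intervals that are too narrow.* The only interval in that section is for median survival. The point is conditional: whatever intervals accompany the coefficients or predictions would ignore selection. The poor coverage figures are for an individual linear predictor, which the SAP does not plan to report. For coefficients the loss is modest.
- *That both SOFA codings enter the model, or that creatinine and eGFR duplicate each other.* The SOFA codings belong to a descriptive list, and the SAP does not say which creatinine feeds baseline eGFR.
- *That leaving allocation out is an error.* The stated aim is a curve for survivors as a cohort, so including allocation is optional.

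The size of the effect also depends on the case chosen. At 250 deaths a continuous factor with HR 1.30 per SD passes 94% of the time. In one simulated setting (all candidates positively correlated at 0.2, all effects in one direction) no real factor was lost and coverage was 96%. However, 97% of null factors also passed there, so the screen did not screen. Finally, the 94% to 95% coverage belongs to a model with all 20 candidates and cannot be credited to a shorter list.

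The objection does not remove the loss of moderate factors or the instability. Pre-specifying the threshold fixes the procedure but not the covariates.

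**Conclusion.** The concern holds for the adjusted Cox model only. Selection by univariable p <= 0.01, with nothing forced in and an ill-defined pool, is a poor rule. With an assumed 162 to 324 deaths among the 810 day-90 survivors, it keeps a binary factor of 20% prevalence 30% to 63% of the time at HR 1.5 and 11% to 25% at HR 1.3. Under the simulated assumptions the selected set is also unstable.

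These sizes rest on assumed deaths, effect sizes, prevalence and correlations. The wording about survivors points to the smaller population. If all randomized patients are modelled (about 900 deaths assumed), retention rises to 99% and 72%. The point is worth correcting because a better rule costs almost nothing. It gives no reason to doubt the comparison by allocation.

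**What to change.** Delete the univariable screen and name a short covariate set before analysis, taken from baseline data already in the RENAL database. Always include accepted prognostic factors such as age, APACHE III and severe sepsis. Use one coding per construct: for example eGFR or the below-60 indicator but not both, and operative status in place of the two diagnosis lists. State the population modelled and how patients with missing covariates are handled.

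One possible set is age (two-parameter spline), sex, APACHE III, severe sepsis, mechanical ventilation, SOFA cardiovascular domain, operative status and eGFR. That is nine parameters, or ten if RENAL allocation is added, which is optional. Ten parameters leave 162/10 = 16 deaths per parameter at the lowest assumed count. The choice of covariates is for the investigators; what matters is that it is fixed in advance.

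If a data-driven step is kept, report bootstrap inclusion frequencies and use intervals that allow for selection.

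The change is to SAP wording and needs no new data. The small downside is that a few weak covariates may be retained.
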